#### Inclusion criteria

Patients with Bell' s palsy meeting the following inclusion criteria are enrolled in the study: involvement of unilateral facial nerve paralysis only, aged between 18 and 75 years old, period of onset of facial paralysis within 72 h.

#### Exclusion criteria

Patients with any of the following are excluded: pregnancy, breastfeeding, being a woman of child bearing age who is unwilling to use contraceptives during the medication period, other neurological diseases, diabetes, badly controlled hypertension, current or history of serious heart disease, history of renal or hepatic disease, gastric or duodenal ulcer, history of glaucoma, acute otitis or history of ipsilateral chronic otitis, history of tuberculosis, history of immunodeficiency syndromes, recent head injury, psychiatric disease, or any other condition that is at risk of being influenced by the study medication or that might have affected completion of the study.

### Randomization

Patients are to be randomly assigned to one of six treatment groups. A computer-generated allocation sequence (in permuted blocks with a block size of 12) will be created by an operator who is not directly involved with the study. Once created, the allocation sequence will be kept in a secure locked drawer making it inaccessible to all study personnel. Allocation concealment will be achieved using sequentially numbered sealed envelopes which are opaque when held to the light. When a patient is enrolled in the study, an independent researcher will be contacted and asked to give the next numbered envelope to the physician who will make up the medications to be used in the study. The independent researcher will record the patient's details and the number of the envelope assigned to that patient. This procedure ensures that the randomization is not influenced by the researchers taking part in this study.

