### Interventions

Patients will be randomized to one of six treatment arms: placebo prednisolone, prednisolone, placebo prednisolone plus acupuncture (acute stage), prednisolone plus acupuncture (acute stage), placebo prednisolone plus acupuncture (resting stage), or prednisolone plus acupuncture (resting stage) within 72 h after onset of Bell's palsy.

Drug treatment: Prednisolone as 5 mg tablets will be given within 72 h after onset of Bell's palsy as a single dose of 40 mg daily for 5 days; the dose will then be reduced by 10 mg per 5 day, with a total treatment time of 20 days.

Acupuncture therapy: On the basis of previous studies, the acupuncture points used will be Dicang (ST4), Jiache (ST6), Yangbai (GB14), Xiaguan (ST7), Taiyang (EX-HN5), Quanliao (SI18) and Yifeng (TE17) on the affected side, and Hegu (LI4) bilaterally. A qualified acupuncturist will give the acupuncture in every center. For acute stage acupuncture, shallow puncturing will be used at facial acupoints and routine puncturing will be used at other acupoints within 72 h after onset of Bell's palsy. Yifeng (TE17), Hegu (LI4) will be punctured 0.5-1.0 cun, the others will be punctured 0.1-0.3 cun. For resting stage acupuncture, penetrative needling will be used from Dicang (ST4) to Jiache (ST6) and from Taiyang (EX-HN5) to Quanliao (SI18) 2-3 cun, and routine puncturing will be used at other acupoints 7 d after enrolment. Filiform needles (33 - 49.5 mm, 0.32 mm) will be used with moderate stimulation to get an acupuncture sensation, and the needles will be retained for 30 minutes, once a day, five times a week, for a total period of four weeks. The locations of those points are defined in 1993 by the World Health Organization (WHO), Regional Office for the Western Pacific [15].

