Central randomization is used in our trial, which is a strict, complete randomization, and it ensures adequate concealment. During the whole trial, the patients are not aware of which group they are to be assigned to, but they do know they will receive acupuncture treatment at different path-stages. Additionally, this trial is a multicenter randomized controlled study, with six months' follow up, containing a large number of patients. Up to now, our trial is one of the largest randomized controlled trials addressing the effectiveness of prednisolone in combination with staging acupuncture treatment for Bell's palsy.

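### Allocation is called complete randomisation but uses one fixed, published block size of 12 with unmasked acupuncture; randomly varied, undisclosed block sizes would be better

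*Protocol article*

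**What the plan says.** Protocol article, Randomization: "Patients are to be randomly assigned to one of six treatment groups". The sequence is described as "A computer-generated allocation sequence (in permuted blocks with a block size of 12", which is two places per arm, or four for each of no acupuncture, acute-stage and resting-stage acupuncture. Concealment is by envelope: "Allocation concealment will be achieved using sequentially numbered sealed envelopes which are opaque when held to the light". The list itself is protected: "the allocation sequence will be kept in a secure locked drawer making it inaccessible to all study personnel". At enrolment an independent researcher is "asked to give the next numbered envelope to the physician who will make up the medications to be used in the study".

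Protocol article, Discussion: "Central randomization is used in our trial, which is a strict, complete randomization, and it ensures adequate concealment". The same section expects recruitment to finish by December 2011, so the block size was disclosed for a trial still described as recruiting.

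Protocol article, Interventions: "A qualified acupuncturist will give the acupuncture in every center". No sham needling is described. Acute-stage needling begins within 72 h of onset and resting-stage needling 7 days after enrolment.

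Protocol article, Patients and enrolment: 1200 patients, from 16 county hospitals and one further hospital. The article does not say whether there is one sequence for all 17 or one for each.

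**The concern.** Two things are wrong as written or less good than they could be.

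First, in statistical usage complete randomisation means unrestricted assignment, in which past allocations carry no information about the next. Permuted blocks do not have that property. The Discussion therefore claims a strength that the procedure in the Randomization section lacks.

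Second, a single known block size is the form of blocking that gives most away when treatment is visible. The locked list and opaque envelopes stop anyone reading the next allocation. They do not stop inference from earlier ones: once all the places of a category in a block are used, the remaining places can be narrowed down. Needling is visible to hospital staff, so the acupuncture category of past patients becomes known locally. If staff could foresee the next category, they could enrol selectively, and the acupuncture comparison would be open to selection bias. The placebo-controlled prednisolone comparison is not exposed through the sight of needling.

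**Working it through.** The article gives no figure for predictability, so there is none to reproduce. The question is how much a fixed block of 12 reveals.

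**Inputs from the article.** Six arms; block of 12; 1200 patients; 16 + 1 = 17 hospitals.
**Assumptions.** Equal recruitment: 1200/17 = 70.6 patients, or 70.6/12 = 5.9 blocks, per hospital. The observer records every earlier patient and knows where each block starts. All three acupuncture categories are visible at once (relaxed in step 4).

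**1. Certain allocations, one sequence per hospital.** A place is certain when all remaining places in the block belong to one category. With three categories of 4, the expected number per block is the sum over j = 1 to 4 of 3 × C(4,j)/C(12,j):
- j = 1: 3 × 4/12 = 1.0000
- j = 2: 3 × 6/66 = 0.2727
- j = 3: 3 × 4/220 = 0.0545
- j = 4: 3 × 1/495 = 0.0061

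The total is 1.333 per block, and 1.333/12 = 11.1%. A hospital with 70 patients completes five blocks and 10 places of a sixth. That gives 5 × 1.333 + (0.0545 + 0.0061) = 6.73, and 6.73/70 = 9.6%. A simulation of such hospitals gave 9.7%. This is the source of about 10%.

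**2. Correct guesses.** The observer names the category with most places left. With t places left and counts x, the expected number correct is G(x) = max(x)/t + Σ (x_i/t) G(x with x_i reduced by 1). For counts 4, 4, 4 this gives 51.2% over complete blocks, against 33.3% by chance; for 70 patients per hospital the simulation gave 50.2%.

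**3. A coarser question.** For acute-stage against everyone else (4 and 8 places), the expected number certain is Σ C(8,j)/C(12,j) + Σ C(4,j)/C(12,j) = 1.60 + 0.44 = 2.04 per block, or 17.0%. Correct guesses are 71.7%, against 66.7% from always naming the larger group.

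**4. Effect of the 7-day delay.** Until day 7, resting-stage patients look like patients without acupuncture. The accrual rate is not given, so the number still unclassified is assumed. With one, two or three of the latest non-acute patients unclassified, the 11.1% falls to 8.4%, 6.4% or 5.2%.

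**5. One sequence shared by 17 hospitals.** Each hospital sees only its own patients. Simulation gives 34.3% correct guesses against 33.3%.

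**6. Varied block sizes.** Simulation, 70 patients per hospital, three visible categories, and an observer who knows the possible sizes but not their order:

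| Sequence | Correct guesses | Certain |
|---|---|---|
| Fixed 12 | 50.2% | 9.7% |
| Random 6/12/18 | 49.8% | 2.3% |
| Random 12/18/24 | 47.5% | 1.4% |
| Complete randomisation | 33.3% | 0% |

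The gain is almost entirely in removing certain allocations. The set without the minimum block of 6 does better on both measures.

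**The case against.** The strongest reply is that every sizeable figure needs per-hospital sequences, which the article never states. The Randomization section speaks of one sequence, one operator, one drawer and an independent researcher who is contacted at enrolment; the Discussion says central. Read together, these favour a single list, for which predictability is close to nil. That stands, and it is why the figures above are conditional.

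A reader might infer that the two sections also contradict each other on central allocation. They do not strictly do so: an independent party who holds numbered envelopes, releases them in order and logs each one can be a form of central allocation. How envelopes reach 17 hospitals, and whether the list is stratified by hospital, are details an article may leave to the full protocol.

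A reader might also infer that staff can time enrolment to obtain a wanted category. The 72 h limit for inclusion leaves little room to hold a patient back. Selective non-enrolment remains conceivable, but nothing in the article shows that it happens.

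Nor is the 17.0% in step 3 the better measure of exposure. It answers a less informative question: 1.60 of the 2.04 certain calls per block say only that the next patient is not acute-stage.

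Finally, complete may be loose praise in a Discussion, and a block of 12 is twice the minimum for six arms. Both are fair. Neither makes the word correct, and neither is a reason to keep a single disclosed size when varied sizes are readily available.

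**Conclusion.** The point holds as a minor one. What is firm is that the Discussion's complete randomisation is not what the Randomization section specifies, and that one fixed, disclosed block size is a weaker choice than varied sizes when acupuncture is unmasked.

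The size is conditional. With one sequence per hospital, about 70 patients each and diligent tracking, at most about 10% of three-way acupuncture categories are certain in advance, and fewer once the 7-day delay is allowed for. With a single shared list the effect is negligible. The article does not settle which applies, although its wording leans towards one list. It does not support a conclusion that allocation is predictable in this trial or that selection bias has occurred.

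**What to change.** For patients not yet randomised, have the independent operator generate the remaining sequence in randomly varied block sizes that are not disclosed to sites, for example 12, 18 and 24, avoiding the minimum block of 6. Under the per-hospital assumption this takes certain allocations from about 10% to about 1–2%; correct guesses fall only from about 50% to about 47.5%. Under a single list little changes either way.

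In the Discussion, replace the claim of complete randomisation with permuted-block randomisation, so that it agrees with the Randomization section.

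The cost is one regenerated list, one wording change and slightly less exact arm balance. A block of 24 holds four places per arm, so two arms can differ by up to 4 within an unfinished block, against 2 with blocks of 12. That is small beside arms of 200 (1200/6).

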### Interventions

Patients will be randomized to one of six treatment arms: placebo prednisolone, prednisolone, placebo prednisolone plus acupuncture (acute stage), prednisolone plus acupuncture (acute stage), placebo prednisolone plus acupuncture (resting stage), or prednisolone plus acupuncture (resting stage) within 72 h after onset of Bell's palsy.

Drug treatment: Prednisolone as 5 mg tablets will be given within 72 h after onset of Bell's palsy as a single dose of 40 mg daily for 5 days; the dose will then be reduced by 10 mg per 5 day, with a total treatment time of 20 days.

Acupuncture therapy: On the basis of previous studies, the acupuncture points used will be Dicang (ST4), Jiache (ST6), Yangbai (GB14), Xiaguan (ST7), Taiyang (EX-HN5), Quanliao (SI18) and Yifeng (TE17) on the affected side, and Hegu (LI4) bilaterally. A qualified acupuncturist will give the acupuncture in every center. For acute stage acupuncture, shallow puncturing will be used at facial acupoints and routine puncturing will be used at other acupoints within 72 h after onset of Bell's palsy. Yifeng (TE17), Hegu (LI4) will be punctured 0.5-1.0 cun, the others will be punctured 0.1-0.3 cun. For resting stage acupuncture, penetrative needling will be used from Dicang (ST4) to Jiache (ST6) and from Taiyang (EX-HN5) to Quanliao (SI18) 2-3 cun, and routine puncturing will be used at other acupoints 7 d after enrolment. Filiform needles (33 - 49.5 mm, 0.32 mm) will be used with moderate stimulation to get an acupuncture sensation, and the needles will be retained for 30 minutes, once a day, five times a week, for a total period of four weeks. The locations of those points are defined in 1993 by the World Health Organization (WHO), Regional Office for the Western Pacific [15].

### Outcomes

In order to reduce outcome assessment bias, the investigators should be given specific training for facial grading, and both the Sunnybrook and House-Brackmann scales will be used.

#### Primary outcome

The primary outcome measurement in this study is the recovery of facial function before randomization and 7 days, 17 days, 1 month, 2 months, 3 months, and 6 months after randomization. Facial function will be assessed at all visits with two grading systems (The Sunnybrook system and The House-Brackmann scale). If recovery is complete (Sunnybrook scale score of 100 points) at 2 or 3 months, the next follow-up grading will be at 6 months.

#### Secondary Outcome

Pain around the ear, in the face, or in the neck will be registered on a visual analogue scale that ranges from 0 to 10 points, where 0 is no pain and 10 very severe pain. Occurrence of facial spasm or contracture and synkinesia in the different treatment arms at any time will be observed and recorded.

### Statistics

The study will be performed using intention to treat. In this analysis, all randomized patients will receive at least one therapy, but patients who did not start treatment will be excluded (modified intention-to-treat analysis). The last-observation-carried-forward method will be used for the modified intention-to-treat analysis. The missing data points will be imputed in the post-baseline follow-up visits from the last observation available for each patient. An interaction test was done to show the synergistic effect of the combination of prednisolone and acupuncture. Categorical variables will be compared by using Fisher's exact test. Cox proportional hazards models will be used to estimate the hazard ratio (HR) of recovery, including 95% CI. These will be compared between groups by using t-test, and Mann-Whitney, or Chi-squared tests as appropriate. All statistical assessments are two-sided, and a P value < 0.05 is considered statistically significant.

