**Methods/Design:**

In this article, we report the design and protocol of a large sample multi-center randomized controlled trial to treat Bell's palsy with prednisolone and/or acupuncture. In total, 1200 patients aged 18 to 75 years within 72 h of onset of acute, unilateral, peripheral facial palsy will be assessed. There are six treatment groups, with four treated according to different path-stages and two not. These patients are randomly assigned to be in one of the following six treatment groups, i.e. 1) placebo prednisolone group, 2) prednisolone group, 3) placebo prednisolone plus acute stage acupuncture group, 4) prednisolone plus acute stage acupuncture group, 5) placebo prednisolone plus resting stage acupuncture group, 6) prednisolone plus resting stage acupuncture group. The primary outcome is the time to complete recovery of facial function, assessed by Sunnybrook system and House-Brackmann scale. The secondary outcomes include the incidence of ipsilateral pain in the early stage of palsy (and the duration of this pain), the proportion of patients with severe pain, the occurrence of synkinesis, facial spasm or contracture, and the severity of residual facial symptoms during the study period.

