## Background

Bell's palsy is an acute peripheral unilateral facial weakness or paralysis with an as yet unknown cause. Bell's palsy accounts for almost three quarters of peripheral facial palsies and the annual incidence is about 30 patients per 100 000. 71% of untreated patients with Bell's palsy will completely recover and 84% will have complete or near normal recovery. The remainder will have persistent moderate to severe weakness, facial contracture, or synkinesis [1-3]. Because of its unclear etiology, there has been longstanding controversy about what treatment should be given, with potential alternatives including corticosteroids, antiviral drugs, acupuncture and physiotherapy. Inflammation of the facial nerve is the most probable cause of Bell's palsy. Therefore corticosteroids are commonly used as treatment of Bell's palsy. A recent study shows significant short-term and long-term positive treatment effects of prednisolone in patients with Bell's palsy [4].

Acupuncture is a safe therapy with a low risk of adverse events in clinical practice [5]. It is one of the most commonly used treatments for Bell's palsy in China. Chinese traditional acupuncture is low cost and very convenient to local people. Though only limited experience has been reported with acupuncture for Bell's palsy [6], several studies provide increasing evidence for a beneficial effect of acupuncture as an adjunctive treatment of Bell's palsy [7-10]. Bell's palsy has different path-stages; it includes acute stage (1-7 days onset of disease), resting stage (8-20 days onset of disease) and restoration stage (21-90 days onset of disease) [11-14]. However, convincing evidence for the efficacy of staging acupuncture to treat Bell's palsy is lacking because of previous poor study designs, small sample sizes or unclear reporting treatment. It's not clear whether acupuncture is effective in different path-stages.

Thus, in view of these data, we designed this randomized controlled multicentre study of Bell's palsy patients, with the aim of comparing the effects of prednisolone and staging acupuncture in the recovery of the affected facial nerve. We also hoped to verify whether staging acupuncture along with prednisolone is more effective than prednisolone alone in larger number of patients, especially in terms of reducing their level of incapacity and improving their quality of life.

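### Last observation carried forward, set as the missing-data rule for the whole main analysis, records unrecovered dropouts as unrecovered to 6 months and so understates recovery in each arm; its relation to the Cox model is left open

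*Protocol article*

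**What the plan says.** The Statistics section of the protocol article sets one rule for missing data: "The last-observation-carried-forward method will be used for the modified intention-to-treat analysis". It then gives the mechanics: "The missing data points will be imputed in the post-baseline follow-up visits from the last observation available for each patient". The same paragraph plans a time-to-event model, "Cox proportional hazards models will be used to estimate the hazard ratio (HR) of recovery, including 95% CI", along with Fisher's exact, t, Mann-Whitney and chi-squared tests. It does not say which of these use filled data.

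The abstract defines the endpoint: "The primary outcome is the time to complete recovery of facial function". Under Primary outcome, facial function is graded before randomization and at "7 days, 17 days, 1 month, 2 months, 3 months, and 6 months after randomization". One visit skip is planned: "If recovery is complete (Sunnybrook scale score of 100 points) at 2 or 3 months, the next follow-up grading will be at 6 months".

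On the course of the disease, the Background says "71% of untreated patients with Bell's palsy will completely recover" and names a "restoration stage (21-90 days onset of disease"). Patients and enrolment assumes 70% complete recovery on placebo, 80% on active treatment, and 15% dropout.

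**The concern.** LOCF is unbiased only if status stays fixed after the last visit, or if later changes cancel out. In Bell's palsy, on the protocol's own account, change runs mostly one way, towards recovery, and much of it falls after the early visits. A patient last graded at 7 or 17 days with residual palsy has a good chance of recovering by 6 months, but LOCF enters a non-recovery at every later visit.

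Two things are at stake. First, recovery proportions and facial scores at each visit are too pessimistic in every arm, and a true difference between arms is diluted. Second, if arms lose patients at different rates, the arm with more dropout looks worse for that reason alone. Some imbalance is conceivable, because four arms require needling five times a week for four weeks (5 × 4 = 20 sessions) and two require none.

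The Cox model adds a question. Its standard treatment of a patient lost before recovery is to censor at the last attended visit. A patient whose later visits are filled in as not recovered would instead stay in the risk set to 6 months as an observed non-event.

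**Working it through.** The protocol reports no figure for the effect of LOCF, so there is none to reproduce. It also gives no recovery curve, no dropout timing and no dropout by arm. These are assumed below and varied.

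**Inputs from the protocol.** Complete recovery p = 70% (placebo) or 80% (treated); six post-baseline visits; 15% dropout; 1200 patients in six groups, so 200 per group.

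**Assumptions.** Cumulative recovery of 5, 15, 30, 50, 60 and 70% at the six visits, scaled by 80/70 for a treated arm. Dropout is unrelated to outcome. The last attended visit is equally likely to be baseline or any of the first five follow-up visits.

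**Step 1: recovery recorded for dropouts.** Mean recovery at the last attended visit = (0 + 5 + 15 + 30 + 50 + 60)/6 = 26.7% when p = 70%, and 26.7 × 80/70 = 30.5% when p = 80%.

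**Step 2: recovery rate under LOCF**, with dropout d: p(1 − d) + d × (mean from step 1).

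**Step 3: equal 15% dropout.**
- Placebo: 0.70 × 0.85 + 0.15 × 0.267 = 63.5%.
- Treated: 0.80 × 0.85 + 0.15 × 0.305 = 72.6%.
- Difference: 9.1 points instead of 10.
- Under the null both arms fall equally, so type I error stays near 5%.
- Power of a two-proportion test at 200 per group falls from 63.8% with complete data to about 49%. With 170 completers per group (200 × 0.85) it would be 56.8%, so part of the loss comes from the missing data and not from LOCF.

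**Step 4: unequal dropout, as a stress scenario only.** With no true effect and p = 70%, the false difference is (gap in d) × (70 − 26.7).

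| Dropout | False difference | Two-proportion test, 200 per arm | Log-rank test on LOCF-filled data |
|---|---|---|---|
| 12.5% vs 17.5% | 0.05 × 43.3 = 2.2 points | about 7% | about 7% |
| 10% vs 20% | 0.10 × 43.3 = 4.3 points | about 15% | about 12% |

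The last two columns are rejection rates against a nominal 5%. A log-rank test with censoring at the last attended visit stays at about 5% in both rows.

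With a true 10-point effect, dropout of 10% in control and 20% in treated gives 70.1 − 65.7 = 4.4 points. The reverse gives 75.0 − 61.3 = 13.7 points.

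**Step 5: other curves and timings.** A second calculation used exponential recovery times (mean parameter 30 to 60 days among recoverers), with the last visit ranging from baseline only to 3 months.
- Equal 15% dropout: 70% becomes 59.5 to 68.1%, and the 10-point difference becomes 8.5 to 9.7 points.
- No true effect (75% in both arms), 10% versus 20% dropout: a false difference of 1.4 to 7.5 points.

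**Step 6: Cox model, if filled values enter it.** Simulation with 100,000 patients per arm and the 30-day curve; each pair is dropout spread evenly over visits / concentrated early.
- 70% versus 80%, equal 15% dropout: hazard ratio 1.26 / 1.24 with LOCF, 1.28 with censoring.
- No true effect, 10% versus 20%: 0.93 / 0.86 with LOCF, about 1.00 with censoring.

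**The case against.** The strongest reply is that the Cox problem is inferred. A reader might conclude that the plan contradicts itself by prescribing both LOCF and a Cox model. The text does not support that: nowhere does it say that filled gradings enter the Cox model. LOCF could serve the visit-wise comparisons while the Cox model censors in the usual way, and a journal article may leave its censoring rule to the full plan. This stands. What remains is an ambiguity, because LOCF is tied to the modified intention-to-treat analysis without exception.

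A reader might also infer that the trial's false-positive rate is inflated. That does not follow either. The protocol states a single dropout figure, and with equal dropout the effect is modest dilution with type I error near 5%. The inflated rates need a dropout gap that the document does not give, and the largest rate here comes from a two-proportion test and not from the time-to-recovery analysis.

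Third, LOCF does not mark all dropouts as unrecovered. Those graded as recovered at their last visit are carried forward as recovered, and for the 3-month visit skipped after complete recovery at 2 months carrying forward is sensible.

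Finally, censoring and multiple imputation also assume that dropout is uninformative given the observed data. Patients who stop attending because they have recovered would bias these methods too. This is true and calls for a sensitivity analysis, but it does not rescue LOCF, which is biased even in the favourable case of dropout unrelated to outcome.

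**Conclusion.** The point holds for what the protocol states. LOCF is a fixed rule for the main analysis set, not a detail left open, and it does not fit a disease in which the protocol itself expects most patients to recover over months. It understates recovery in each arm by counting later recoveries among unrecovered dropouts as failures. With equal 15% dropout the loss is 6.5 points on a true 70% (1.9 to 10.5 points over the curves and timings tried), and a 10-point difference shrinks to about 9.1 (8.5 to 9.7).

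The direction of any bias between arms depends on who drops out: dilution if dropout is equal, either direction if it is not. The unequal-dropout figures show sensitivity and are not a forecast. The effect on the hazard ratio is conditional on filled values entering the Cox model. All sizes rest on assumed recovery curves and on dropout unrelated to outcome.

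**What to change.** Replace LOCF as the primary method in the Statistics section:

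- **Time to recovery:** state that patients without recorded recovery are censored at their last attended visit and that no filled values enter the Cox model.
- **Visit-wise recovery proportions and facial scores:** use multiple imputation with arm, baseline grade and all earlier gradings; a mixed model is an alternative for scores.
- **Planned skip:** carry the value forward only for the 3-month visit that the schedule omits after complete recovery at 2 months.
- **Sensitivity:** keep LOCF as a sensitivity analysis, and add one that departs from the assumption that dropout is uninformative given the observed data. Report dropout by arm and by visit.

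The cost is revised wording in the protocol and analysis plan and slightly more programming. No new data are needed. The downside is that the replacement methods carry their own untestable assumption about dropout, which is why the added sensitivity analysis is needed.

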### Patients and enrolment

A power analysis is undertaken to calculate before conducting this trial: α = 0.05 and power = 80%. According to the previous literature, 70% of patients recover completely without treatment (placebo) compared with 80% of patients treated with prednisolone, acupuncture, or both. This difference of 10% is regarded as a clinically significant improvement. Therefore, the sample size in this trial can be estimated initially according to PASS software. Each group needs at least 172 patients (assuming a 15% dropout rate), 1200 patients in six groups will be enrolled in the study.

Baseline assessments before the start of treatment include neurological examination, grading of facial function, measurement of ipsilateral pain, documentation of concurrent medication. Patients with acute, unilateral, peripheral facial palsy, who are referred from neurology, internal medicine or emergency departments, or who seek care directly, are screened by physicians in 16 public county hospitals and Xijing hospital in Shaanxi province. There is at least one experienced neurology physician, who is responsible for implementing the study, with a special interest in facial palsy in each hospital. A written consent form will be obtained from each patient and retained by the investigators.

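### The Statistics section contradicts itself on how recovery is tested: Cox hazard ratios, then t-test, Mann-Whitney or chi-squared tests that do not allow for censoring

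*Protocol article*

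**What the plan says.** The abstract states the primary outcome as a time to event: "The primary outcome is the time to complete recovery of facial function, assessed by Sunnybrook system and House-Brackmann scale". The Primary outcome section words it as a series of gradings: "The primary outcome measurement in this study is the recovery of facial function before randomization and 7 days, 17 days, 1 month, 2 months, 3" (the list of visits ends at half a year). Complete recovery is a Sunnybrook score of 100.

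The Statistics section makes four statements that bear on how recovery is analysed, in this order:

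1. Missing follow-up values in the modified intention-to-treat analysis are filled by last observation carried forward (LOCF).
2. Categorical variables are compared by Fisher's exact test.
3. "Cox proportional hazards models will be used to estimate the hazard ratio (HR) of recovery, including 95% CI".
4. Directly after that sentence comes the one at issue: "These will be compared between groups by using t-test, and Mann-Whitney, or Chi-squared tests as appropriate".

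The Patients and enrolment section expects 70% complete recovery on placebo and 80% on active treatment, with 15% dropout and 1200 patients in six groups.

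**The concern.** The pronoun that opens the fourth statement has the hazard ratio of recovery as its nearest antecedent. A hazard ratio is already a between-group comparison; it is not a patient-level measurement that a t-test or Mann-Whitney test could compare.

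If recovery times are meant, the tests run but are unsuitable. A patient who leaves unrecovered, or is still unrecovered at the last visit, has no recovery time. A t-test or Mann-Whitney test must leave that patient out or enter some other number as the time. If recovered status is meant, the chi-squared test competes with the Fisher's exact test already assigned to categorical variables, and LOCF counts every unrecovered dropout as unrecovered at 6 months.

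The primary comparison could therefore be run in several ways that give different answers, with only *as appropriate* to choose between them. At stake are power and, if dropout differs between arms, the false-positive rate.

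**Working it through.** The protocol gives no figure for the performance of these tests, so there is none to reproduce. Its sample size of 172 per group rests on proportions and is a separate matter.

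**Inputs from the protocol.** 70% vs 80% recovery, 15% dropout, two-sided 5% level; 1200/6 = 200 per arm, or 200 × 0.85 = 170 after dropout; gradings at 7 and 17 days and 1, 2, 3 and 6 months.

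**Assumptions.** Recovery times are exponential. The 70% and 80% apply at 6 months (180 days), since the protocol attaches no time point to them. Dropout is exponential and unrelated to recovery. Recovery is dated to the visit at which it is first seen.

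**Patients without a recovery time.** Even without dropout, 1 − 0.70 = 30% and 1 − 0.80 = 20% are unrecovered at 6 months.

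**Benchmark by formula.** Under proportional hazards, HR = ln(0.2)/ln(0.3) = 1.34, with ln HR = 0.290. Average recovery is 75%, so the events in a two-arm comparison are D = 2 × n × 0.75. Schoenfeld power comes from z = ½ × √D × ln HR − 1.96.

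- n = 200 (no dropout): D = 300, z = ½ × 17.32 × 0.290 − 1.96 = 0.55, power 71%.
- n = 170 (dropouts contribute nothing): D = 255, z = ½ × 15.97 × 0.290 − 1.96 = 0.36, power 64%.

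A log-rank test with dropout spread over follow-up should fall between these values.

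**Simulation, 3000 trials per setting, 200 per arm.** *Observed time* is the visit of recovery or, failing that, the last visit attended. The chi-squared test uses recovered status with LOCF.

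| Setting | Log-rank | Chi-squared | t-test, observed time | Mann-Whitney, observed time |
|---|---|---|---|---|
| 70% vs 80%, 15% dropout in both arms (power) | 66% | 55% | 44% | 42% |
| No effect, 15% dropout in both arms | 5.1% | 5.2% | 4.7% | 4.7% |
| No effect, dropout 10% vs 20% | 5.3% | 12.9% | 18.1% | 16.6% |
| No effect, dropout 5% vs 25% | 4.8% | 37.5% | 58.1% | 56.0% |

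The simulation standard error is √(0.44 × 0.56/3000) = 0.9 points for the t-test's power and √(0.18 × 0.82/3000) = 0.7 points for its 18.1%. The log-rank power of 66% lies between the two benchmarks.

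A second simulation on the same assumptions gave 68% power for log-rank, 44% for the t-test on observed time, and 53% for a t-test with unrecovered patients set to 180 days. With no effect and 10% vs 20% dropout, it gave 19% rejections for the t-test on observed time and 6% for log-rank.

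**Direction of the error.** In the arm with more dropout, observed times are cut short, so a t-test sees faster recovery. In the same arm, LOCF leaves fewer patients counted as recovered, so a chi-squared test sees worse recovery. Two tests allowed by the same sentence are thus biased in opposite directions.

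**The case against.** The strongest reply is that the plan already holds a valid comparison. A Cox hazard ratio with a 95% CI compares groups and handles censoring, and an interval that excludes 1 serves as a test at the 5% level. The sentence that follows may be a misplaced reference to other measures: pain on the 0 to 10 scale, facial scores at a visit, or proportions recovered, on which the trial was sized. The named tests can suit such measures.

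Much of this stands. A reader might infer that the plan has no analysis that allows for censoring; the Cox sentence shows otherwise. A reader might also picture a t-test among recovered patients only, which had 13-15% power in the two simulations, but no section plans that analysis, so it does not count towards the size of the problem. Nor does the loss depend only on which test is chosen: setting unrecovered patients to 180 days costs 68 − 53 = 15 points, less than the 68 − 44 = 24 points with observed time.

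A further inference is that the baseline facial grade goes unused. The enrolment section says it is collected: "Baseline assessments before the start of treatment include neurological examination, grading of facial function, measurement of ipsilateral pain". The Statistics section names no covariates, but it does not say that the Cox model is unadjusted. A condensed article commonly leaves covariates to the full plan, and the same holds for centre and tied times. The gain from adjustment cannot be computed from the document.

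The reply does not rescue the sentence itself. Its literal antecedent is the hazard ratio. The charitable reading still has to reconcile chi-squared with Fisher's exact test, and no reading says which analysis decides the primary outcome.

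**Conclusion.** The point holds as a contradiction in a stated rule. Recovery is assigned to Cox models and, in the next sentence as written, to tests that cannot compare hazard ratios and do not allow for censored recovery times.

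If the sentence were applied to observed recovery times, a t-test would have about 44% power against 66-68% for log-rank, a loss of 22 to 24 points. With no effect and 10% vs 20% dropout, its type I error would be about 18-19%.

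These sizes rest on exponential recovery, on reading 70% and 80% as 6-month rates, and on dropout unrelated to recovery. The type I error figures also need unequal dropout; with equal dropout every test stays near 5%. The protocol gives no dropout by arm. Unequal dropout is plausible, because four arms have five acupuncture sessions a week for four weeks (5 × 4 = 20) and two have none, but it remains an assumption.

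**What to change.** Replace the sentence that follows the Cox model with:

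> Time to complete recovery is compared between groups by the test from the Cox model (or the log-rank test), with patients not recovered censored at their last graded visit and not carried forward by LOCF. The t-test or Mann-Whitney test applies only to fully observed continuous measures, such as pain scores at a visit. One named test (Fisher's exact or chi-squared) applies to categorical outcomes.

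One of each pair should be chosen before the data are unblinded. The Primary outcome section should use the abstract's time-to-recovery wording, so that outcome and test match.

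Adjusting the Cox model for the baseline facial grade is an optional improvement, not a correction.

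The cost is wording only. No new data, visits or patients are needed.
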